### Endpoints

#### Primary endpoint

To determine the safety of intraarticular UC-derived WJ formulation (GeneXSTEM^TM^).

#### Secondary endpoints

To assess change in patient-reported outcome measures, NPRS and KOOS, from baseline to various follow-up time points.To assess cartilage formation via MOCART at the 1-year time point and compare if from baseline.To assess patient satisfaction using SF-36, 7-point Likert scale and Single Assessment Numeric Evaluation (SANE).

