### Study design

Twelve patients with grade II/III OA who meet the inclusion and exclusion criteria will be recruited for this non-randomized, open label, multi-center, prospective study. The study will be conducted at two sites within the USA, and the patients will be followed for 1 year, with an expected duration of 15 months (Figs. 1 and 2). Figure 2 depicts the schedule for enrolment, intervention and assessment according to the SPIRIT guidelines.

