### Inclusion criteria

Patients who are 18 years or older with a body mass index (BMI) of < 40 kg/m^2^ and a diagnosis of mild to moderate (grade II/III) OA in only one knee on the KL grading scale will be recruited. Patients must also meet the following criteria:
Pain score of 4 or more on the NPRSWilling and capable of giving written informed consent to participateWilling and capable of complying with study-related requirements, procedures, and visitsFemale patients must be abstinent, surgically sterilized, or postmenopausalPremenopausal females with negative pregnancy test, and who does not anticipate pregnancy and will actively practice an accepted contraceptive method for a duration of the studyMales with premenopausal female partners will take contraceptive measures for the duration of the study

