### Study intervention

After patients are determined to be eligible for the study during visit 1 (preliminary/baseline), they will receive an intraarticular injection of UC-derived WJ (GeneXSTEM^TM^) by the site PI during Visit 2.1 (procedure).

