### Assessment points

Assessments for the study period will start at visit 1 (preliminary/baseline) which includes a thorough review of the patient’s inclusion/exclusion criteria and proper documentation of the informed consent form prior to participation. Once these steps are met, participant’s demographic information, medical history, and baseline case report forms (CRFs) such as NPRS, KOOS, 36-item short-form survey (SF-36), and Single Assessment Numeric Evaluation (SANE) will be collected. Baseline plain radiography (Standing AP, Flexion PA (Rosenberg method), Lateral, and Merchant views) for OA grading using the KL scale will be obtained. Participants will also undergo a T2-weighted MRI and receive a Magnetic Resonance Observation of Cartilage Repair Tissue (MOCART) score. Additionally, a comprehensive metabolic profile, liver function tests, complete blood count, markers of inflammation (C-reactive protein, erythrocyte sedimentation rate), T,B and NK cell lymphocyte subsets, and serum IgG, IgA, IgM, and IgE levels will be collected. At visit 2.2, immediately after the injection procedure, and at visits 3 (24-h follow-up) and 4 (48-h follow-up), NPRS will be collected. During visits 5 (1-week follow-up) and 6 (6-week follow-up), CRFs (NPRS, KOOS, 7-point Likert scale, and SANE) will be collected. Participants will also undergo a PE and have their comprehensive metabolic profile, liver function tests, complete blood count, markers of inflammation (C-reactive protein, erythrocyte sedimentation rate), T,B and NK cell lymphocyte subsets, and serum IgG, IgA, IgM, and IgE levels collected. During visits 7 (3-month follow-up) and 8 (6-month follow-up), participants will undergo the same process as well as have plain radiographs (standing AP, flexion PA (Rosenberg method), lateral and merchant views) taken. During the participants’ final visit, visit 9 (1-year follow-up), the same process as in visits 7 and 8 will be undertaken with an additional T2-weighted MRI for a MOCART score. Participants will have opportunities to report any AEs at each visit or at any time during the study.

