### Sample size and statistical analysis

Descriptive statistics will be computed for all study variables. Continuous variables will be described with measures of central tendency (mean, median) and dispersion (range, standard deviation). Categorical variables will be summarized as frequencies and percentages. Comparisons between categorical variables will be compared with the chi-square test; continuous variables will be compared with Student’s *t* test or non-parametric equivalents. Paired continuous data will be assessed with a paired *t* test or Wilcoxon signed rank test, depending on distribution. Paired categorical data will be assessed with McNemar’s test. For the longitudinal data, a mixed-model repeated measures analysis will be used to examine the between subject factors and the within subject factor of time (baseline, visit 1, visit 2, etc.), as well as their interaction, on the outcome variables of interest. Post hoc tests with corrections for multiple comparisons will be run to determine where significance lies. *P* values < 0.05 will be considered statically significant.

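### The cartilage-formation endpoint compares a repair-tissue score with a pre-treatment baseline in knees where no repair tissue or target region is defined, so the change cannot be read as cartilage formation

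*Protocol article*

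**What the plan says.** In the protocol article, Secondary endpoints includes the aim "To assess cartilage formation via MOCART at the 1-year time point and compare if from baseline". Assessment points gives the two measurements. At visit 1, before the injection: "Participants will also undergo a T2-weighted MRI and receive a Magnetic Resonance Observation of Cartilage Repair Tissue (MOCART) score". At visit 9, one year on, the visit is repeated "with an additional T2-weighted MRI for a MOCART score".

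Inclusion criteria selects patients with a "diagnosis of mild to moderate (grade II/III) OA in only one knee on the KL grading scale". Under Study intervention, "they will receive an intraarticular injection of UC-derived WJ"; no cartilage repair procedure is part of the trial. Study design describes a "non-randomized, open label, multi-center, prospective study", and "Twelve patients with grade II/III OA who meet the inclusion and exclusion criteria will be recruited". No comparator arm is described.

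Better cartilage formation over one year is part of the hypothesis at the end of Background and is repeated in Discussion. The Abstract lists cartilage regeneration among the improvements to be assessed. For before-after comparisons, Sample size and statistical analysis says: "Paired continuous data will be assessed with a paired *t* test or Wilcoxon signed rank test, depending on distribution".

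**The concern.** A change score needs the same quantity measured on both occasions. MOCART is named for repair tissue, yet its first reading comes before any treatment, in knees not selected for having had a repair. It is unclear what that reading rates, so it is also unclear what a rise a year later would mean.

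MOCART is the only imaging measure in the list of secondary endpoints. In an open-label trial without a described comparator, readers will tend to take it as the objective evidence. The article says the results should prepare the ground for a large placebo-controlled trial, so a structural result that cannot be interpreted could carry over into that design.

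A subsidiary concern is the reading of the scans. The two MRIs are taken a year apart and there is no concurrent control. Drift or expectation in the readings would add directly to the before-after difference unless the reading procedure prevents it.

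**Working it through.** **Part 1: instrument against construct (no arithmetic applies)**

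- What the score rates: repair tissue, by the expansion of the acronym in Assessment points and Abbreviations.
- When it is first applied: visit 1. The injection follows at visit 2.1.
- Who is scored: patients with KL grade II/III osteoarthritis in one knee. Neither a previous repair nor a focal defect is an entry requirement. Exclusion criteria rules out index-knee surgery only within the last 6 months, so an older repair is possible but not required.
- What is done to the knee: an intraarticular injection.
- Where the score is applied: no lesion, compartment or region is named.
- What is concluded: cartilage formation, from the 1-year score compared with baseline.

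The first five items leave the baseline score without a defined object. The difference between a 1-year score and such a baseline has no defined object either. The last item therefore does not follow, even if every step is carried out exactly as written.

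**Part 2: how far a reading shift could matter (illustration only)**

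The article gives no effect size, standard deviation or power for its 12 patients, so there is no planned figure to reproduce.

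Inputs: n = 12 (Study design); paired t test and significance level 0.05 (Sample size and statistical analysis). Assumed here: two-sided testing, 12 complete pairs, normally distributed changes, no true change, and a systematic reading shift δ expressed in SDs of the paired change. The documents give no value for δ.

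1. The critical value on 11 degrees of freedom is 2.201. The smallest observed mean change that reaches significance is 2.201/√12 = 2.201/3.464 = 0.635 SD.
2. With a shift δ and no true change, the test statistic is noncentral t on 11 degrees of freedom with λ = δ√12. The false-positive rate is P(|T| > 2.201).

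| Assumed δ (SD of change) | λ = 3.464 × δ | False-positive rate |
|---|---|---|
| 0 | 0 | 5.0% |
| 0.1 | 0.346 | 6.2% |
| 0.3 | 1.039 | 15.8% |
| 0.5 | 1.732 | 35.3% |

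A simulation of 200,000 trials gave 5.0% at δ = 0 and 35.5% at δ = 0.5, in agreement. With only 10 complete pairs, the rates at δ = 0.1 and 0.5 are 5.9% and 29.3%.

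**The case against.** The strongest objection concerns scan reading. A reader might infer from the two visit-linked scores and the open-label design that each scan is read at its own visit by someone who knows which is post-treatment. The article does not say so. It states when the scans are acquired and that a score is given, and it is silent on reader, session, order and masking. Masked paired reading is possible in a single-arm trial, and a journal article commonly leaves such detail to the full protocol or an imaging manual. The objection stands: reader bias is not shown, and the silence is not itself a fault. The false-positive rates depend on assumed shifts; at 0.1 SD the effect is small, and the plan also allows a Wilcoxon test.

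Other stronger readings also fail:

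- That none of these knees has ever had a repair. Surgery more than 6 months earlier is not excluded.
- That the osteoarthritis is diffuse. The article does not say so.
- That MOCART is the trial's only outcome not reported by patients. Physical examinations, laboratory tests and radiographs are also collected; MOCART is only the sole imaging measure named among the secondary endpoints.
- That cartilage thickness or T2 values could be taken from the planned scans. The article specifies only a T2-weighted MRI, which does not establish this.

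It can also be said that this is one secondary endpoint in a 12-patient study whose primary endpoint is safety, and that the argument rests on the score's name because the article gives no scoring detail. Both are fair and limit the weight of the point. They do not remove it: the article itself fixes the instrument, both time points and the conclusion, and these do not fit together.

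**Conclusion.** The point holds for the instrument. As written, the plan would report a change in a repair-tissue score as cartilage formation, although no repair tissue or target region is defined at baseline. The measure does not support that conclusion. This rests on the article's own expansion of the score, its entry criteria and its intervention, and on no outside source. It affects a secondary endpoint and one of the stated hypotheses; the primary safety aim is untouched.

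The mismatch has no numerical size. The rates of about 6%, 16% and 35% concern only a possible reading shift of assumed size. They are a reason for masked reading and not evidence that bias is present.

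**What to change.** 1. Label the MOCART comparison exploratory, and remove the cartilage-formation hypothesis and conclusion that rest on it from Background, Secondary endpoints and Discussion. Alternatively, if the acquired MRI sequences support it, replace MOCART with a whole-knee osteoarthritis cartilage score named in advance. Sequence suitability must be confirmed before choosing this option.
2. In either case, state that each patient's baseline and 1-year MRIs are read together after visit 9, de-identified, in random order and masked to date. If the full protocol or an imaging manual already says this, one sentence referring to it is enough.

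Cost: relabelling is a change of text and costs almost nothing. Masked paired reading needs no extra visit or scan, but research scores become available only at study end. A replacement score needs a different scoring form, and a change of sequence if the planned one does not support it. The structural claim also becomes weaker.

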### Sample size and statistical analysis

Descriptive statistics will be computed for all study variables. Continuous variables will be described with measures of central tendency (mean, median) and dispersion (range, standard deviation). Categorical variables will be summarized as frequencies and percentages. Comparisons between categorical variables will be compared with the chi-square test; continuous variables will be compared with Student’s *t* test or non-parametric equivalents. Paired continuous data will be assessed with a paired *t* test or Wilcoxon signed rank test, depending on distribution. Paired categorical data will be assessed with McNemar’s test. For the longitudinal data, a mixed-model repeated measures analysis will be used to examine the between subject factors and the within subject factor of time (baseline, visit 1, visit 2, etc.), as well as their interaction, on the outcome variables of interest. Post hoc tests with corrections for multiple comparisons will be run to determine where significance lies. *P* values < 0.05 will be considered statically significant.

### Data collection and handling

The PI will maintain all source documents. The data will be duplicated on paper study CRFs, and the PI will secure original data in order to be made available to the sponsor and study monitors. Hard copies of CRFs and media will be stored in a secure location and maintained by the PI for a period of 7 years. CRFs will be available for initial inspection for omitted data, data inconsistencies, illegible data, and deviations by the study monitors.

The PI will be responsible for submitting data and reports as follows:
AEs: in an ongoing basis. This will be reported in the proper section of the CRF.Severe AEs: report within 24 h of knowledge of event to sponsor and report to IRB within 5 days as per their regulations.Deviations, exceptions, violations of protocol: report to sponsor within 5 days and report to IRB per their regulations.Protocol progress report: provide a copy to sponsor and IRB as per regulations.Study closure report: provide a copy to sponsor and IRB as per regulations.

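### Expedited safety reporting is triggered by severe, not serious, adverse events, so a serious event of lesser intensity has no stated reporting deadline

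*Protocol article*

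**What the plan says.** The protocol article's section Data collection and handling lists what the site PI must report and when. Two items concern adverse events:

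- The general item reads "AEs: in an ongoing basis. This will be reported in the proper section of the CRF". It carries no time limit.
- The expedited item reads "Severe AEs: report within 24 h of knowledge of event to sponsor", and it adds a report to the IRB within 5 days, subject to the IRB's own regulations.

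The same list gives protocol deviations a 5-day limit for reaching the sponsor.

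On capture, Assessment points says: "Participants will have opportunities to report any AEs at each visit or at any time during the study". The primary endpoint is "To determine the safety of intraarticular UC-derived WJ formulation".

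The article gives no definition of a severe adverse event, no intensity scale for adverse events and no class of serious adverse events. *Serious* appears only in an exclusion criterion about neurological and psychiatric disorders. The abbreviation list has an entry for adverse events but none for serious ones.

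**The concern.** Severity and seriousness are separate attributes of an adverse event. Severity grades how intense the event is. Seriousness, by the usual convention, depends on what it leads to: death, threat to life, hospitalisation, disability and similar consequences. Expedited reporting exists so that those responsible for participants hear quickly about events of consequence, so its trigger should be seriousness. The trigger written here is severity.

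What is at stake is the timeliness of oversight. The Background says that clinical literature on the safety of these products is limited or absent, and the Discussion places the trial among the first of its kind. There is little outside experience to fall back on, so prompt notice of a serious event matters more than usual.

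**Working it through.** No arithmetic applies: the article gives no figure to reproduce, and the point rests on no sample size, event rate or alpha. The check is a reading of the rule.

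**Step 1. Is the term defined or corrected elsewhere?** Every mention of adverse events, *severe* and *serious* was read, in the Background, Exclusion criteria, Assessment points, Primary endpoint, Data collection and handling, Discussion and Abbreviations. None defines a severe adverse event or replaces the term. The only other use of *severe*, in the Background, describes the degree of osteoarthritis by grade, which is the ordinary sense of degree rather than consequence.

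**Step 2. Apply the rule literally to the four possible kinds of event.**

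| Event | Route as written | Stated deadline to sponsor |
|---|---|---|
| Serious and severe | Expedited | 24 h |
| Severe, not serious (e.g. an intense but harmless pain flare) | Expedited | 24 h |
| Serious, not severe (e.g. a hospitalisation for an event of moderate intensity) | CRF, ongoing | None |
| Neither | CRF, ongoing | None |

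The third row is the gap.

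**Step 3. Compare with the rest of the list.** A protocol deviation must reach the sponsor within 5 days. A serious but non-severe event has no stated limit. An order of urgency that puts a deviation ahead of a hospitalisation is unlikely to be intended.

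**Step 4. Does another stated route close the gap?** For these events the instruction is "This will be reported in the proper section of the CRF". The CRFs are on paper and are kept by the PI. Study monitors may inspect them, and Quality control and assurance gives the sponsor, monitors and regulators access to CRFs and medical records. No timing is stated for any of this, so none of it substitutes for a 24-hour trigger.

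**Step 5. Does the gap reach the primary endpoint data?** No. Participants can report any event at any visit or in between, and all events go on the CRF. The counts that describe safety remain available whichever route an event takes.

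**The case against.** The strongest objection is that *severe* is a slip for *serious*. A 24-hour report to the sponsor, followed by one to the IRB, is typical of serious-event reporting, and the full protocol, which is not shown, may use and define the right term. The article gives no intensity grades, so the third row of the table assumes a grading that it does not set out. This stands as a limit on certainty: the wording does not prove that any event would be reported late. It does not remove the point. An article may leave definitions to the full protocol, but this one states a trigger, and the word it uses is the wrong one. If it is a slip, the correction is the same.

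It can also be said that the reference to IRB regulations brings serious events in. That phrase qualifies the IRB report within the severe-event item and leaves the 24-hour sponsor trigger unchanged.

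A reader might infer more than the article supports:

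- *That safety tables would miss serious events.* Nothing says that tables will be built on the severe class. The rule concerns who is told and when, not analysis.
- *That the CRF lacks fields for seriousness, severity or relatedness.* The CRF is not shown, and a condensed article need not describe its fields.
- *That the defect can be sized from the sample.* The Study design section says "Twelve patients with grade II/III OA who meet the inclusion and exclusion criteria will be recruited", so one event would be 1/12 = 8.3% of participants. That describes a hypothetical event rate. It does not say how often a serious event would be judged non-severe or how long notice would be delayed.

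**Conclusion.** The point holds as a wrong trigger term in stated text. As written, expedited reporting depends on intensity, and a serious event that is not severe falls to a route with no deadline, where the sponsor would otherwise hear within 24 hours and the IRB within 5 days.

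The consequence is confined to the timeliness of sponsor and IRB oversight. It matters here because safety is the primary endpoint and prior clinical experience is thin. No estimate, test or adverse event count changes, so it does not undermine the validity of the primary endpoint. No numerical size can be attached.

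The conclusion assumes that *severe* carries its ordinary meaning of intensity and that sites would follow the published wording. If the full protocol already uses and defines *serious*, only the article's wording is at fault. This is a moderate correction.

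**What to change.** In Data collection and handling, make the trigger for the 24-hour sponsor report and the 5-day IRB report: *Serious AEs (meeting any standard seriousness criterion), whatever their severity*. Severe non-serious events can stay on the 24-hour route if the sponsor wishes. The sponsor should also confirm that the full protocol uses the same term and defines it.

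The cost is a one-line amendment and a note to the one or two sites. It adds no burden for participants and leaves treatment, assessments and analysis unchanged.

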### Quality control and assurance

Documents and data will be produced and maintained to ensure control and protection of the patient’s privacy. The protocol, CRFs, and medical records will be available for access by the Sponsor, study monitors, and representatives of regulatory authorities. All attempts will be made to preserve the patient’s privacy and confidentiality.

## Discussion

OA is the most common joint disorder in the USA. It causes significant pain and loss of function for patients and leads to significant strain on the healthcare system [1]. The knee is the most commonly affected joint, and current treatments of OA focus on decreasing pain, increasing function, and improving quality of life. These treatments, however, fail to effectively resolve the underlying pathophysiological processes involved in OA or regenerate diseased cartilage. This is one of the many reasons why the field of regenerative medicine and the use of biologics including UC-derived WJ have grown so rapidly.

This trial will be one the first to evaluate the safety and efficacy of intraarticular UC-derived WJ with patients with grade II or III knee OA. We anticipate that the intraarticular injection of UC-derived WJ is safe, and participants will show an improvement in their overall satisfaction, pain, function, and quality of life. We also hypothesize that cartilage formation over a period of 1 year compared to the baseline visit will improve. Positive outcomes from this study will also lay the foundation for a large placebo-controlled trial of intraarticular UC-derived WJ for symptomatic knee OA.

